#### **16.4.2 Young person participants (15<18years inclusive)**

For eligible young person participants (15<18 years), a parent/ legal guardian will be present and give consent for the young person to participate. Consent will also be obtained from the young person. Both parent/legal guardian consent and child consent will be given to be eligible for participation.

It will be pointed out to the parent/legal guardian that consent can be withdrawn at any time without prejudice and withdrawal will not affect current treatment. The participant and parent/legal guardian will have the opportunity to ask questions. A telephone number will be provided so that the participant and parent/legal guardian can call a research representative who will be able to respond to any questions they may have.

If the parent/legal guardian withdraws consent, regardless of the continuing young person's consent, then the young person will be withdrawn from the study.

If the young person's consent is withdrawn, regardless of the parent/legal guardian consent, then the young person's decision will be respected and they will be withdrawn from the study. This is to protect the young person's emotional wellbeing and continued ongoing routine care.

Each participant and parent/ legal guardian will acknowledge receipt of this information by giving written informed consent for participation in the study. The consent forms will be signed and dated by a witness. A notation that written informed consent has been obtained will be made in the participant's Case Report Form (CRF). The completed consent forms will be retained by the Investigator and a copy will be provided by the research staff to the participant.

#### **16.5 Participant Reimbursement**

Participants will be reimbursed for out of pocket expenses, inconvenience and time involved by the provision of prepaid gift cards (e.g. Coles-Myer, K-Mart etc). We will provide a \$40 gift card at the end of week 2, and mid-way through the protocol (week 6) and on completion (week 12) (total reimbursement \$120). If the study is terminated by the Investigator prior to completion, or a participant withdraws or is withdrawn from the study before completion, a pro-rata payment will be made at the discretion of the Investigator.

#### **16.6 Emergency Contact with Investigators**

All participants will be provided with a Participant Emergency Contact Card with contact details of whom to contact in the case of an emergency including unblinding.

#### **16.7 Notification of Primary Care Physician and Treating Psychiatrist**

With the consent of the participant, the Investigator will notify the primary care physician (provided that such a physician can be identified for the participant) and treating Psychiatrist of the participants' involvement in the study. A letter will be sent to the physician and treating Psychiatrist stating the nature of the study, treatments, expected benefits or adverse events. A copy will be retained by the study site for verification by the Study Monitor.

## **16.8 Investigator Indemnification**

The clinical trial insurance will reimburse participants for costs of medical care that occur as a result of complications directly related to participation in this study. The Investigator and insurance company will be notified as soon as possible if this occurs or where a causal relationship cannot be excluded. All SAE's will be reported to the nominated insurance company.

The University of Queensland (Sponsor) will enter into a Clinical Trial Agreement with each of the five Hospital and Health Services (HHS's) involved in the study, based on the standard Medicines Australia format.

## **16.9 Intellectual Property (IP) and Licencing**

The collection of data in this study is subject to Intellectual Property (IP) and Licencing agreements which will be documented in the Research Agreement.

## **16.10 Publication Policy**

Results will be disseminated in peer reviewed publications and published in international journals. There will be an undertaking to seek journals that have open access policies. Our findings will also be summarised in several brochures, including one designed for feedback to participants and Hospital and Health Services (HHS's) who participate in the study. Only group data will be reported.

## **16.11 Protocol Amendments**

Any amendments to the protocol will be submitted to the appointed HREC by the Chief Investigator for approval. Any approved amendments by the appointed HREC will be forwarded by the Chief Investigator for submission to each Research Governance Office.

No changes (amendments) to the Protocol will be implemented without prior approval from the Reviewing Ethics Committee. If a Protocol amendment requires changes to the Informed Consent Form, the revised Informed Consent Form, prepared by the Chief Investigator, will be approved by the Reviewing Ethics Committee and site governance officers.

Once the final Protocol has been issued and signed by the Chief Investigator and the authorised signatories, it will not be informally altered. All protocol amendments will pass through appropriate approval steps before being implemented. Any change to the protocol constitutes an amendment.

Where the amendment affects the ongoing suitability of the study at a participating site, Research Governance approval will also be sought. The Research Governance Office will determine the ongoing suitability based on the amendment submitted.

The Chief Investigator will submit the amendment to the appointed HREC for their approval; written approval will be obtained. Completed and signed Protocol amendments will be circulated to all appointed site Investigators.

The original signed copy of amendments will be kept in the Study File with the original Protocol. Where an amendment to the Protocol substantially alters the study design or the potential risks to the participants, each participant's consent to continue participation will be obtained.

## **16.12 Version Control**

Version control ensures that amendments to documents are tracked and verifiable and that the correct version of a document is in use according to the relevant ethical, regulatory or local approval.

All documents will be given a version number and date e.g. Version 1.0 15-Feb-15

Each amendment to a document will require a version number and date to be updated.

If this is a **significant change** e.g. change in the content of the document, then the version number will be increased by 1.0.

If it is a **minor change** e.g. contact details, then the number after the decimal point will be increased by 0.1.

## **16.13 Protocol Compliance**

Should there be questions or consideration of deviation from the Protocol, clarification will be sought from the Study Monitor. Any participant treated in a manner that deviates from the Protocol, or who is admitted into the study but is not qualified according to the Protocol, will be ineligible for analysis.

If an emergency occurs that requires a departure from the Protocol, the nature and reasons for the Protocol violation/deviation will be recorded in the CRF and the Chief investigator will notify the Reviewing HREC and /or Governance Office as soon as possible.

Whilst the Chief Investigator has overall responsibility for the conduct of the study, the appointed site Investigators will have the responsibility to ensure all study personnel at their sites comply with GCP, National Statement on Ethical Conduct (2007), Australian Code for the Responsible Conduct of Research and local policies and procedures.

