**Table 1: Schedule of Visits and Assessments**

**Assessment schedule can vary plus or minus five days for operational convenience**

| Visit                                       | 0
Screening
Phase | 1
Baseline | 2 | 3 | 4 | 5 | 6 | 7 | 8 | 9 | 10 | 11 | 12 | 13 | 14 |
|---------------------------------------------|-------------------------|---------------|---|---|---|---|---|---|---|---|----|----|----|----|----|
| WEEK                                 |                         | 0             | 1 | 2 | 3 | 4 | 5 | 6 | 7 | 8 | 9  | 10 | 11 | 12 | 14 |
| Study medication period(12 weeks)    |                         |               |   |   |   |   |   |   |   |   |    |    |    |    |    |
| SCREENING AND CONSENT                |                         |               |   |   |   |   |   |   |   |   |    |    |    |    |    |
| Assessment of current medication            | X                       |               |   |   |   |   |   |   |   |   |    |    |    |    |    |
| Informed consent                            | X                       |               |   |   |   |   |   |   |   |   |    |    |    |    |    |
| Ongoing capacity                            |                         | X             | X | X | X | X | X | X | X | X | X  | X  | X  | X  |    |
| Inclusion / exclusion criteria              | X                       |               |   |   |   |   |   |   |   |   |    |    |    |    |    |
| Urine pregnancy test (females only)         | X                       |               |   |   |   |   |   |   |   |   |    |    |    |    |    |
| Drug dispensation (after randomisation)     |                         | X             |   | X |   | X |   | X |   | X |    | X  |    |    |    |
| SAFETY                               |                         |               |   |   |   |   |   |   |   |   |    |    |    |    |    |
| Adverse events                              |                         |               |   | X | X | X | X | X | X | X | X  | X  | X  | X  | X  |
| Physical health and metabolic measures      |                         | X             |   | X |   | X |   | X |   | X |    | X  |    | X  |    |
| EFFICACY                             |                         |               |   |   |   |   |   |   |   |   |    |    |    |    |    |
| PANSS TOTAL SCORE                           | X                       | X             |   | X |   | X |   | X |   | X |    | X  |    | X  |    |

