## **8.9 Overdose**

An overdose is defined as a dose taken by a patient in excess of the doses in the approved study protocol or available product information, either accidentally or intentionally, irrespective of whether it involves study medication or non-study medication. Overdose may be suspected or confirmed and may or may not be associated with clinical signs and symptoms.

It would definitely include (but not be limited to) those events which based on the investigators clinical judgment were considered to be of medical concern and /or require clinical observation and /or medical intervention. An overdose would include any dose greater than the highest daily dose included in the protocol or available product information. Deviations to study drug administration (i.e. resulting from poor patient compliance) which do not meet the definition of an overdose, will be recorded in the study medication compliance section of the case Report Form (CRF) and not as Serious AE's.

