### 1006 **9.2 Participant Withdrawal by the Investigator**

1007 Patients will be withdrawn from the study by the Investigator, prior to completion of treatment,  
1008 under the following conditions:

- 1009 • Non-compliant with study medication for seven consecutive days
- 1010 • Development of a serious adverse event assumed to be associated with the study  
1011 medication
- 1012 • Cessation of effective contraception or confirmed pregnancy
- 1013 • Continual inability to provide informed consent.

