### **11.4 Statistical Analysis**

All data will be analysed using SAS 9.4. We will compare demographic and clinical differences between the groups at baseline (Fisher exact test for nominal variables and Mann-Whitney test or independent sample  $t$  test for continuous variables). Efficacy will be assessed according to standard Intention to Treat (ITT) analytic procedures (i.e. for those who do not complete the 12 week study period, we will carry forward their last observation on the study outcomes). Mean changes in clinical assessment will be assessed using mixed-model repeated-measure (MMRM) methods with treatment, week, and treatment-week interaction as fixed effects and intercept as the only random effect; baseline value will be the covariant. The MMRM analyses will be performed using the SAS PROC Mixed procedure.  $P$  values will be based on 2-tailored tests with significance levels of 0.05.

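### Section 16.13 removes participants whose treatment deviated, and ineligible entrants, from analysis; Section 11.4 specifies intention to treat, and the protocol does not say which rule governs the primary analysis.

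*Protocol*

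**What the plan says.** Protocol Section 11.4 sets the principle for efficacy: "Efficacy will be assessed according to standard Intention to Treat (ITT) analytic procedures". It then says what happens to early leavers: "for those who do not complete the 12 week study period, we will carry forward their last observation on the study outcomes". So a participant who stops early stays in the analysis.

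Protocol Section 16.13, among the administrative procedures, sets a different rule. It covers "Any participant treated in a manner that deviates from the Protocol, or who is admitted into the study but is not qualified", and its consequence is that such a participant "will be ineligible for analysis". It is not limited to major deviations or to a per-protocol or sensitivity set. It does not ask for the decision to be made blind or before database lock.

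Two other sections bear on whom 16.13 reaches. Section 8.9 speaks of "Deviations to study drug administration (i.e. resulting from poor patient compliance) which do not meet the definition of an overdose" and has them recorded as compliance data. Section 9.2 lists among the grounds for withdrawal by the investigator "Non-compliant with study medication for seven consecutive days". Non-adherence is therefore foreseen, and the protocol itself calls it a deviation.

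**The concern.** The same participant can be kept by one section and removed by the other, and nothing gives either section precedence. The choice decides who enters the trial's only primary comparison.

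The two groups named in 16.13 do not carry the same risk:

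- **Participants whose treatment deviated.** Adherence is seen after randomisation and can depend on tolerability, symptoms and therefore arm. Removing these participants can make the remaining groups differ for reasons other than treatment.
- **Entrants who did not qualify.** Eligibility turns on facts that precede randomisation, so removing these entrants is less prone to bias. It still departs from ITT, and 16.13 does not require the judgement to be made without knowledge of allocation or outcome.

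If the conflict stays open, it could be settled after results are known, and a reader could not tell which analysis set had been pre-specified. Numbers are a secondary matter: Section 11.3 allows for 15% attrition and for no loss through 16.13.

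**Working it through.** **Step 1: the two rules side by side**

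| Participant | Section 11.4 | Section 16.13 |
|---|---|---|
| Withdrawn under 9.2 after seven days of non-compliance | Kept, last observation carried forward | Removed, on a natural reading with 8.9 |
| Poorly adherent, stays to week 12 | Kept | Removed, on the same reading |
| Randomised but found not to qualify | Kept under ITT | Removed, explicitly |

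The conflict is textual and needs no arithmetic.

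**Step 2: the plan's own sample size**

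Inputs from Sections 11.3 and 11.4: difference 7, SD 14.3, two-sided alpha 0.05, power 0.80, 1:1 allocation, attrition 15%.

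- d = 7/14.3 = 0.4895.
- n per arm = 2(1.960 + 0.842)²/d² = 65.5, so 66 per arm and 132 in total. This matches the plan. The t-test version gives 66.5, so 67.
- 132/0.85 = 155.3, so 156, consistent with the plan's approximate 160.

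**Step 3: power if 16.13 is applied**

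Power is from the two-sample t-test with non-centrality d√(n/2), n per arm. For example, n = 80 gives 0.4895 × √40 = 3.10 and power 0.868. The documents give no deviation rate, so the exclusion rates are assumed.

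| Assumed exclusion | From 160: n per arm | Power | From 136: n per arm | Power |
|---|---|---|---|---|
| 0% | 80 | 0.868 | 68 | 0.809 |
| 15% | 68 | 0.809 | 58 | 0.743 |
| 20% | 64 | 0.785 | 54 | 0.712 |
| 30% | 56 | 0.728 | 48 | 0.660 |

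The 160 base follows 11.4, which keeps non-completers. The 136 base is 160 × 0.85. Its per-arm numbers are rounded from 57.8, 54.4 and 47.6, and it may count some people twice, because withdrawals for non-compliance could already be part of the 15%.

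**Step 4: illustration of bias with no true effect**

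Assume 80 per arm, exclusions in one arm only (a fraction f), and excluded participants m points worse than that arm's overall mean. The kept mean then shifts by f·m/(1 − f).

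- f = 0.05, m = 7: 0.35/0.95 = 0.37 points; type I error about 0.053.
- f = 0.10, m = 10: 1.00/0.90 = 1.11 points. The standard error is 14.3 × √(1/72 + 1/80) = 2.32, and type I error is about 0.077.
- f = 0.15, m = 10: 1.50/0.85 = 1.76 points; type I error about 0.116.

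If m is measured against those kept instead, the shift is f·m. The middle case becomes 1.0 point and about 0.07. Both f and m are assumptions.

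**The case against.** The best reply is that 11.4 is the dedicated statistical section, names ITT and gives a rule for non-completers, whereas 16.13 is a general compliance clause among administrative procedures. A sensible analyst would follow 11.4. A statistical analysis plan, not shown here, may also define the analysis sets. This has force as a prediction of conduct. It does not remove the conflict: 16.13 is operative text, and Section 16.11 treats any change to the protocol as an amendment. An analysis plan would have to depart from one of the two rules.

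Four stronger readings are tempting and go beyond the documents:

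- *The primary analysis has become per-protocol.* That assumes 16.13 overrides 11.4, which the text does not say. The analysis set is ambiguous.
- *Every deviation, however small, leads to exclusion.* The clause concerns how a participant was treated. The five-day tolerance in Table 1 concerns assessments ("Assessment schedule can vary plus or minus five days for operational convenience"), so a late visit is not clearly caught. Taking vitamin C above the limit in Section 6.3 is also unclear. Missed capsules are the stronger case because of 8.9. Even that can be argued, since 7.10 has compliance calculated for use in the analysis, which suggests imperfect adherence among those analysed.
- *All the exclusions rest on post-randomisation behaviour.* That is not so for ineligible entrants.
- *The trial would be underpowered.* From 160, a 15% exclusion still leaves 0.81. Power falls below 0.80 only at higher assumed rates or from the 136 base.

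Section 7.7 also withholds allocation from investigators and study personnel until database lock, emergencies aside. This limits deliberate selection if exclusions are settled by then, but the protocol does not require that timing. Blinding would not cure bias from deviations that treatment itself causes.

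**Conclusion.** The point holds as a contradiction between 11.4 and 16.13 over who is in the primary efficacy analysis. It needs correcting because 16.13, if followed as written, would remove randomised participants partly on behaviour after randomisation.

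The size cannot be derived from the documents. Over assumed exclusions of 15% to 30%, power runs from 0.81 down to 0.73 on the 160 base, which fits 11.4 better, and from about 0.74 down to 0.66 on the 136 base. Under the assumed one-sided exclusions in Step 4, type I error is between about 0.053 and 0.116. These figures show what is possible and do not forecast it. The conclusion rests on the wording and on reading 16.13 together with 8.9, not on any of these rates.

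**What to change.** Amend 16.13 to say that:

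1. all randomised participants are included in the primary efficacy analysis in the arm to which they were allocated, whatever deviations or eligibility errors occurred;
2. deviations and eligibility errors are recorded and listed;
3. any exclusion under 16.13 applies only to a supportive per-protocol set, fixed before unblinding.

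A cross-reference from 11.4 would make the precedence plain. The minimum needed to remove the contradiction is item 1; item 3 gives the existing exclusion rule a defined and harmless place. How to treat randomised participants with no PANSS score after baseline is a separate detail that the analysis plan can settle.

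The cost is a short protocol amendment, with ethics committee approval and forwarding to each governance office under Section 16.11. Treatment, visits and data collection do not change.

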## **16.14 Archives: Retention of Study Records**

All Case report Forms (CRF's) and study documentation will be kept by the Investigators for at least 15 years or the maximum time frame as determined by local regulations, whichever is the longest.

